### Frequency and duration of follow-up

All participants will be followed up at 4 and 12 months post-randomisation. There will be one additional data collection point at 8 months with the carer alone, to chart any changes in the participant’s medication use and receipt of services.

### Outcome measures

#### Quantitative assessments

An overview of data collected at baseline and 4 and 12 months post-randomisation is shown in Table 1. Additionally, a purpose-specific questionnaire to gather demographic and health data about participants, and the participants’ expectations of therapy, will be completed at baseline only. Carers will also be telephoned at 8 months post-randomisation to complete the Client Service Receipt Inventory (CSRI).

**Table 1 Tab1:** Outcome measure assessments

Outcome	Participant measures	Carer measures
Depressive and anxiety symptoms	Glasgow Depression Scale for People with Learning Disabilities (20 items: 10 minutes)	Intellectual Disabilities Depression Scale (38 items: 10 minutes)
	Glasgow Anxiety Scale-ID (20 items: 10 minutes)	
Aggression		The Behaviour Problems Inventory for Individuals with Intellectual Disabilities; Aggressive Behaviour sub-scale (10 items: 5 minutes)
Carer self-efficacy	Not applicable	Emotional Difficulties Self-Efficacy Scale (10 items: 5 minutes)
Participant-carer relationship	Not applicable	Expressed Emotion: Five-Minute Speech Sample
Activity measures and quality of life	EuroQual (EQ-5D 3 L; 5 items: 5 minutes)	EQ-5D 3 L (5 items: 5 minutes)
	Social Support Questionnaire (3 items: 10 minutes)	Modified Index of Community Involvement (46 items: 10 minutes)
		Modified Index of Domestic Participation (13 items: 5 minutes)
		ABS-RC:2 (4 sub-scales; 48 items; 10 minutes)
Response to life events	Bangor Life Events Schedule for Intellectual Disabilities (24 items: 10 minutes)	Not applicable
Health economics	EQ-5D (5 items: 5 minutes)	EQ-5D (5 items: 5 minutes)
		Client Service Receipt Inventory (30 items: 10 minutes)
		Medication inventory (10 items: 5 minutes)

### Quantitative outcome evaluation

#### Primary outcome measure

This will be a measure of depressive symptoms by using the Glasgow Depression Scale for People with Intellectual Disabilities (GDS-LD) [19]: This is a 20-item self-rating scale that requires the participant to indicate how often a particular symptom has occurred by using a 3-point scale (never/sometimes/always) during the previous week.

#### Secondary outcome measures

The Intellectual Disabilities Depression Scale (IDDS) [25] will provide an informant view of the clients’ depressive symptoms and will be completed by the carer. This is a checklist of behavioural symptoms of depression that can be observed by an informant. Other emotional and inter-personal difficulties that might be associated with depression will also be examined. Anxiety symptoms will be measured by using the Glasgow Anxiety Scale-ID (GAS-ID) [26], and aggressive behaviour will be measured by using the Behaviour Problems Inventory (BPI) [27].

Perceived and actual life changes that might be influenced by the interventions will also be examined, including Social Support using the Social Support Questionnaire (SSQ3) [28]. Changes in social and community-based activities will be measured by using the Index of Community Involvement (ICI) [29] and the Index of Participation in Domestic Life (IPDL) [30] aiming to capture changes in participation in household tasks. The Adaptive Behavior Scale - Residential and Community: Second Edition (ABS-RC2) [23] will be used as a proxy measure of avoidance of activity, a key aspect of behavioural change targeted by the behavioural activation treatment.

Patient-carer relationship will be assessed by using the Expressed Emotion: Five-Minute Speech Sample (FMSS) [31], and Carer Self-Efficacy will be examined by using the Emotional Difficulties Self-Efficacy Scale (EDSE) [32, 33]. This is a flexible scale to assess carer perceptions of their self-efficacy in specific support domains relating to adults with intellectual disability.

Finally, life events are recorded by using the Bangor Life Events Schedule for Intellectual Disabilities (BLESID) Self-Report [34] version. The BLESID will allow analysis of the potential changes in response to life events over time (e.g., reduced negative impact of new life events experienced during the course of the study), and recent exposure to life events (prior to screening assessment) will be included as a potential moderator of outcome in exploratory analyses. As this questionnaire has been developed to allow individuals to report on life events that have occurred over the last 12 months, it will be administered at baseline and 12-month follow-up only.

### Qualitative component

Up to 15 participants from each arm of the trial (n = 30) and 10 carers who attended therapy sessions in each arm of the trial (n = 20) will be interviewed. Participant and carer interviews will be guided by a semi-structured interview schedule. The questions will address the participants’ views and experiences of the Beat-It and Step-Up therapies in order to develop a better understanding of the change process. This part of the research is not hypothesis-driven. Instead, the main aim is to gain an ‘insider’s perspective’ that will assist with the interpretation of the quantitative results and help with the translation of the research findings into everyday practice. Focus groups of six study therapists from the Beat-It arm of the trial will also be held after all treatment is finished, to explore their experience of delivering the therapy and perceived barriers and successes.

#### Health economic evaluation

The economic analysis will be based on recorded health-related quality of life and health-care resources collected as part of the study. In keeping with UK guidance for conducting health economic evaluations, the EuroQoL instrument (EQ-5D Y) [35] will be used. A modified version of the EQ-5D Y will be used for the participants with intellectual disabilities. This version has more straightforward language aimed at young people who are at least 7 years old. However, the language is not “child-like” and so is appropriate for people with intellectual disabilities. The cost of delivery of the intervention itself will be based on timesheets that are collected as part of the study for the health service staff involved in the delivery of the intervention, costed at the mean of the relevant staff grade. The CSRI [36] will be used to record other health service contacts such as visits with community-based primary care, other health or social services, educational services, and outpatient and inpatient attendances. Unit costs will be taken from published UK reference costs. In combination with the CSRI, medication use will also be recorded and costed (Medication Inventory). Cost per quality-adjusted life-year of the BEAT-IT intervention will be calculated and results presented on the cost-effectiveness plane with statistical uncertainty represented by using confidence intervals or cost-effectiveness acceptability curves as appropriate.

#### Process evaluation

To establish fidelity to the Beat-It treatment, up to two randomly assigned sessions will be video- or audio-recorded with the permission of patients and their carers. One recording will be from the initial assessment phase (sessions 2–5) and a second from the active treatment phase (sessions 6–12). The recordings will be reviewed by an independent rater against a checklist of core requirements for (i) adherence to the manual, (ii) therapeutic process, and (iii) therapeutic alliance. The checklist has been adapted from an existing fidelity instrument, the Manualised Group Intervention Check [37], developed for group interventions and taking into account the particular social and communication skills required when working with people who have intellectual disabilities. Raters will be trained to a high level of initial reliability and then their ratings of session recordings will periodically be checked for drift.

Up to two recordings of the guided self-help attention control intervention, taken from initial sessions 2–5 and closing sessions 6–8, will also be reviewed as described above. The fidelity checks for the guided self-help intervention will cover the same non-specific elements of therapy as the Beat-It evaluation.

#### Data collection and blinding

The two treatments are of similar lengths and both involve a supporter meeting with the therapist alongside the patient. These similarities help to reduce the chance of the research assistants inadvertently finding out whether the patient has received behavioural activation or guided self-help, if patients make reference to their therapy in their meetings with the therapists. Other precautions include ensuring that none of the researchers carries out qualitative interviews with participants they are collecting data from or are involved with fidelity checks for them. Records will be kept of any instances of the researchers being unblinded and reported in research publications. The final statistical analysis plan will be subject to detailed review by a statistician who does not have access to the study data or randomisation schedule.

### Data analysis

#### Quantitative outcomes

The primary analysis will compare GDS-LD scores at 12 months post-randomisation between intervention groups, adjusting for baseline GDS-LD scores, study centre and use of anti-depressants at baseline within a mixed-effects linear regression model, including therapist as a random effect. Similar methods will be applied to the primary outcome measure at the immediate post-intervention assessment (4 months post-randomisation) and to secondary outcome measures at all assessment points. Repeated measures analysis, adjusting for stratification factors, will also be applied to each outcome measure. Models for the primary outcome will be extended to explore the effects of baseline characteristics, including the stratification factors, chronicity of depressive symptoms, life events, and history of previous failed psychological intervention. The moderating effects of these factors will be explored by using appropriately constructed interaction terms within linear regression models. These moderation analyses will be exploratory only and designed to inform future translation of the intervention into routine clinical practice. Similarly, we will also carry out exploratory analyses focused on potential mediation effects. In particular, changes to 4 months post-randomisation can be explored as mediators of effects to follow-up at 12 months post-randomisation, and therapist-rated session data can be used to explore potential mediators that may change within the therapeutic process.

### Qualitative outcomes

The interviews will be analysed by using framework analysis. This is a structured form of qualitative data analysis initially developed by the National Centre for Social Research [38] and designed for applied research. Rather than themes and sub-themes being wholly emergent from the data, framework analysis allows the researcher to start with a set of *a priori* themes which are used as an initial guide to the analysis, although in the analysis these themes can be altered and new themes can emerge from the data. Framework analysis is less labour-intensive than many other types of qualitative data analysis and allows for the systematic examination of data from relatively large samples for qualitative analysis.

For this study, the major *a priori* themes to begin the framework analysis will concern a number of dimensions that may inform the future uptake of intervention in clinical practice. These will include the following: participants’, carers’, and therapists’ perspectives on the process of change; helpful and unhelpful aspects of the interventions; factors relating to the three-way working relationship and the carer-patient relationship and barriers and facilitative factors relating to the maintenance of the interventions after cessation of contact with the therapist. Data from the focus group will be included in the framework analysis as additional evidence.

### Health economic outcomes

In the initial pilot stage, the contribution of the health economics element will be confined to ensuring that the appropriate data collection of resource use is made to support a full economic evaluation of the trial if the study proceeds to the second stage. The full economic analysis will compare the costs of the treatment with the quality-of-life benefits as measured by the EQ-5D in the 12-month post-randomisation follow-up period. The difference between treatment and control will be adjusted for any baseline differences in EQ-5D.

In addition, consideration will be given to potential cost-offsets associated with the treatment in terms of both direct costs to health and personal social services and direct costs to the patient and their carer [39]. The base case perspective will be the NHS and personal social services supplemented by a broader analysis that considers patient/carer costs. There are two components to the estimation of direct health service costs. The first is the costing of the treatments (behavioural activation therapy and the guided self-help) where the principal cost for these will relate to the time required to deliver the intervention. The second part of the costing will be to establish other service resource use and for that we will use the CSRI and the medication checklist. During the set-up phase, we will explore whether this format needs to be adapted for use with this population. The societal perspective will be assessed very simply as the time burden associated with participants and their carers attending for contacts with health/social services. Uncertainty in cost, quality-adjusted life-year (QALY) [40], and cost-per QALY estimates will be handled statistically through the use of non-parametric bootstrapping during the period of the trial. Extensive sensitivity analysis will be used to explore issues around whether unit costs might be somewhat different for patients with intellectual disabilities, the grade/salary of staff delivering the intervention and the number of sessions they can deliver per week, and the impact on cost-effectiveness of alternative assumptions concerning the durability of any treatment effect beyond the 12 months post-randomisation follow-up.

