**Fig. 1 Fig1:**
[figure not shown]
Flow diagram for the Beat-It study

In the first 18 months of the open trial of BEAT-IT, the mean (standard deviation, or SD) reduction in the Glasgow Depression Scale for People with Learning Disabilities (GDS-LD) [19] scores at 3-month post-intervention follow-up was 8.50 (5.24). We have powered the study to detect a mean between-group difference of 0.6 SD units, or 3.14 points on the GDS-LD. This makes the conservative assumption that the 4-month post-randomisation difference in score between the intervention and control groups will be 60 % of that observed from pre-test to follow-up in the open trial, thereby allowing for some improvement in the control arm of the trial, or for the observed improvement in the open trial being an overestimate of what will be achieved in a randomised trial, or for both. To have 90 % power to detect this effect size difference, the study requires 60 patients in each arm to provide outcome data at 12 months post-randomisation. The primary analysis will be an analysis of covariance adjusting for the baseline GDS score, which will have power to detect smaller intervention effects, depending on the level of correlation in scores over time.

There are no data to inform the effect of clustering of outcomes for patients seen by each therapist. Assuming that each therapist works with an average of nine participants (i.e., several part-time therapists at each site) and assuming an intraclass correlation of 0.025, the sample size must be increased by 20 % to 72 per group, or 144 in total. Recruitment of 166 participants will allow for up to 13.3 % loss to follow-up.

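### The economic comparison names baseline EQ-5D as its only adjustment, leaving out baseline cost and the randomisation strata, and does not carry therapist clustering into its uncertainty analysis

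*Protocol article*

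**What the plan says.** Under Health economic outcomes, the protocol article compares costs with EQ-5D-based benefits over the 12 months after randomisation. On adjustment it says: "The difference between treatment and control will be adjusted for any baseline differences in EQ-5D". On uncertainty it says that cost, QALY and cost-per-QALY estimates will be "handled statistically through the use of non-parametric bootstrapping during the period of the trial". Baseline cost, centre, antidepressant use and therapist are not mentioned there, and the unit of resampling is not given.

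Other sections bear on this:

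- Quantitative assessments: "An overview of data collected at baseline and 4 and 12 months post-randomisation is shown in Table 1". Table 1 lists the Client Service Receipt Inventory (CSRI) and the medication inventory.
- Randomisation: the two stratification variables are study centre and use of antidepressants.
- Sample-size text under Design: "Assuming that each therapist works with an average of nine participants", and "assuming an intraclass correlation of 0.025, the sample size must be increased by 20 % to 72 per group, or 144 in total".
- Treatments: each therapist is trained in one intervention only, so therapists are nested within arm.
- Quantitative outcomes: the primary model adjusts for baseline score, centre and antidepressant use, "including therapist as a random effect".

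**The concern.** There are two separate issues, and they act on the cost interval in different directions.

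**Adjustment.** If a person's service cost before randomisation predicts the cost afterwards, leaving it out of the cost model discards precision that the data could supply. It also lets a chance imbalance in prior service use pass into the incremental cost. The strata are a similar case: they shaped the allocation and are in the clinical model, but are not named for the economic one.

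**Clustering.** The trial enlarges its sample for therapist effects and models them for the clinical outcome. Intervention cost is built from therapists' timesheets, and the number of Beat-It sessions may vary from 8 to 12, so costs could plausibly cluster by therapist. A bootstrap that treated participants as independent would then understate uncertainty in the cost-effectiveness results. Cost-effectiveness is one of the trial's two stated aims.

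**Working it through.** **1. The plan's own figures.** The plan states: "We have powered the study to detect a mean between-group difference of 0.6 SD units, or 3.14 points on the GDS-LD". With SD 5.24, 3.14/5.24 = 0.60. At 90 % power and two-sided alpha 0.05 (alpha is my assumption; none is stated), the normal approximation gives 59 per arm and the t-based solution 59.35, so 60. This agrees with "To have 90 % power to detect this effect size difference, the study requires 60 patients in each arm".

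Design effect = 1 + (9 − 1) × 0.025 = 1.20. Then 60 × 1.20 = 72 per arm, 144 in total. 1 − 144/166 = 13.3 % loss. All of these reproduce.

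**2. Baseline-cost adjustment.** For a linear covariate with baseline-to-follow-up correlation r, the variance of the adjusted difference is (1 − r²) times the unadjusted one. The documents give no r, so the range is assumed.

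| r | Variance cut (r²) | SE factor √(1 − r²) |
|---|---|---|
| 0.3 | 9 % | 0.95 |
| 0.5 | 25 % | 0.87 |
| 0.7 | 49 % | 0.71 |

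Chance imbalance: with 72 per arm, the SE of a baseline mean difference is √(2/72) = 0.167 SD. An imbalance of one such SE shifts the unadjusted cost difference by r × 0.167, that is 0.05, 0.08 or 0.12 SD of follow-up cost at r = 0.3, 0.5 or 0.7.

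**3. Ignoring therapist clustering.** If individuals are resampled, the bootstrap SE is too small by a factor √DE, where DE = 1 + 8 × ICC. Nominal 95 % coverage becomes 2Φ(1.96/√DE) − 1, and the interval is too narrow by 1 − 1/√DE. No ICC for costs or QALYs is given, so a range is shown around the trial's assumed value.

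| ICC | DE | √DE | Too narrow by | Coverage |
|---|---|---|---|---|
| 0 | 1.00 | 1.00 | 0 % | 95.0 % |
| 0.01 | 1.08 | 1.04 | 3.8 % | 94.1 % |
| 0.025 | 1.20 | 1.095 | 8.7 % | 92.6 % |
| 0.05 | 1.40 | 1.18 | 15.5 % | 90.2 % |
| 0.10 | 1.80 | 1.34 | 25.5 % | 85.6 % |

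**4. Would plain therapist resampling repair this?** With nine participants per therapist there would be about 72/9 = 8 therapists per arm (an assumption). Simulations used normal data, 8 therapists per arm with 9 participants each, ICC 0.025 and percentile intervals:

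- Resampling individuals: coverage 91.1 % to 92.3 % across separate runs.
- Resampling whole therapists: coverage 90.6 % to 91.9 %. Even at ICC 0 it covered only 91.1 %, so the shortfall comes from having few clusters.
- Plain two-stage resampling: coverage 97.9 %, with intervals about 39 % wider.

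Neither plain scheme is a clean remedy.

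**5. The two issues together.** If the ICC stayed at 0.025 after adjustment, the SE relative to an unadjusted analysis that ignores clustering would be √(1.2 × (1 − r²)) = 1.04, 0.95 or 0.78 at r = 0.3, 0.5 or 0.7. The net change could go either way.

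**The case against.** The strongest reply is that this is a condensed article and the analysis plan is not shown. The article does not say that EQ-5D is the sole covariate or that individuals are the resampling unit. A non-parametric bootstrap can be clustered, stratified or regression-based. This stands against two readings that a reader might infer: that the plan has decided to leave out baseline cost, and that it has decided to ignore therapists. It does not dispose of the adjustment point, because the article does fix an adjustment for this comparison and names one covariate where better ones appear to be at hand.

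A second reply is that the clinical methods already cover the economics. The Abstract lists cost-effectiveness among the secondary outcomes, and Quantitative outcomes extends similar methods to secondary outcome measures. This is not clear cover: Secondary outcome measures does not list costs or QALYs, and Health economic outcomes gives them a method of their own.

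A reader might also infer that the economic intervals are too narrow. The documents do not support that. They give no ICC for costs or QALYs, and the sample-size text says that no data exist on clustering by therapist. Omitting baseline cost widens the interval, while ignoring positive clustering narrows it. Nor is the cost difference biased, since allocation is randomised 1:1.

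Finally, the phrase about any baseline differences could be read as adjusting only if an imbalance is seen. That is strained, since it is common wording for routine adjustment; saying that adjustment is always made would remove the doubt.

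One caution stands. Table 1 has no time-point column, and it includes the life-events schedule, which is given at baseline and 12 months only. Baseline CSRI collection is therefore likely, not certain, and its recall period is not stated.

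**Conclusion.** The point holds as a worthwhile improvement to a stated method, not as an error that invalidates the economic analysis.

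On adjustment, naming only baseline EQ-5D leaves precision unused and chance cost imbalance uncorrected. The size is a 9 % to 49 % cut in the variance of the cost difference, resting on assumed correlations of 0.3 to 0.7 and on baseline CSRI and medication data being available.

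On clustering, the economic section does not carry through what the sample-size text and the primary model recognise. The consequence is conditional on individual resampling and a positive ICC for costs or QALYs. At 0.025 it is modest: an SE factor of about 1.10 and coverage of about 92.6 %. At zero there is none. The two parts should not be merged into one statement about interval width.

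**What to change.** In Health economic outcomes, or in the analysis plan that implements it:

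1. Estimate incremental costs and QALYs from regression models that always adjust, whatever imbalance is observed: baseline cost (CSRI plus medication) in the cost model, baseline EQ-5D in the QALY model, and centre and antidepressant use in both.
2. Keep each participant's cost and QALY together in every bootstrap sample.
3. State how therapist is handled, in line with the primary analysis: a therapist random effect, or a method with a small-cluster correction. Do not rely on a plain therapist-level percentile bootstrap, which does not restore coverage with about eight therapists per arm.
4. Confirm that the CSRI and medication inventory are completed at baseline, and state the recall period.

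The cost is wording and a little code, on data that appear to be collected already. The clustering step makes intervals slightly wider (a factor of about 1.10 at ICC 0.025).
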